**6.5.2.2. No concomitant treatment**

Sedatives used for the induction of general anesthesia other than protocol treatment

**6.5.2.3. Treatments that can be used in combination**

**Hypotension**

a) Hypotension with heart rate <80 beats/min, ephedrine 4 mg

b) Hypotension with heart rate ≥80 beats/min, phenylephrine 0.05 mg.

**Bradycardia** (heart rate <45 beats/min)

a) Bradycardia without severe hypotension, atropine 0.5 mg bolus (one additional dose allowed.)

b) Bradycardia with hypotension and ephedrine 4 mg is acceptable in addition to atropine.

**Others**

Drugs for the treatment of complications and adverse events (AEs)

**6.5.3. Criteria for dose reduction and drug withdrawal**

Discontinue the treatment protocol if the physician in charge determines that it is difficult to continue treatment due to the occurrence of AEs.

**6.5.4. Criteria for dose increase and resumption**

Not applicable

**6.5.5. Discontinuation of research in individual research participants**

**6.5.5.1. Discontinuation criteria**

- 1. Participant's request to withdraw consent
  2. Cases that are determined after enrollment to be inappropriate for inclusion because they do not meet the inclusion criteria or conflict with the exclusion criteria
  3. Severe hemodynamic instability (*i.e.*, hypotension with poor response to vasopressor use, severe bradycardia) between anesthesia induction and observation period
  4. In case of difficulty in continuation due to the occurrence of AEs
  5. Serious deviations from the protocol
  6. The decision by investigators and others

**6.5.5.2. Discontinuation procedure**

- 1. If the administration of the trial drug is to be discontinued, the necessary observations, examinations, and evaluation will be made. Participants will be informed after awakening from anesthesia.
  2. Appropriate treatments will be taken for the participant when the administration of the trial drug is discontinued due to the occurrence of AEs or other safety issues. Continue follow-up and document outcomes until symptoms (including laboratory values) return to pretrial drug or baseline status or until symptoms stabilize.
  3. The reason for the discontinuation of administration should be stated in the case report form (CRF).

**6.5.5.3. Posttreatment after discontinuation of protocol treatment**

Not applicable

**7. Observation, examination, investigation, and evaluation items**

**7.1. Participant’s timeline**

|  | **STUDY PERIOD** | | | | | | |
| --- | --- | --- | --- | --- | --- | --- | --- |
|  | **Enrollment** | **Allocation** | **Post-allocation** | | | | **Close-out** |
| **TIMEPOINT*** | **1** | **2** | **3** | **4** | **5** | **6** | **7** |
| **ENROLLMENT:**  **Eligibility screen** | **X** |  |  |  |  |  |  |
| **Informed consent** | **X** |  |  |  |  |  |  |
| **Allocation** |  | **X** |  |  |  |  |  |
| **INTERVENTIONS: *[Remimazolam]*** |  |  |  | **X** |  |  |  |
| ***[Propofol]*** |  |  |  | **X** |  |  |  |
| **ASSESSMENTS:** |  |  |  |  |  |  |  |
| ***Baseline variables***  ***[age, sex, height, weight, medical history, medicines, ASA PS, CFS, surgical procedure, laboratory values]*** | **X** | **X** |  |  |  |  |  |
| ***Vital sings***  ***[blood pressure, heart rate]*** | **X** |  | **X** | **X** | **X** | **X** |  |
| ***Time to loss of consciousness*** |  |  |  | **X** |  |  |  |
| ***Induction drug injection pain*** |  |  |  | **X** |  |  |  |
| ***Dose of trial drugs for induction*** |  |  |  |  |  | **X** |  |
| ***Dose of vasopressors*** |  |  |  |  |  | **X** |  |
| ***AEs and SAEs*** |  |  |  |  |  |  | **X** |

**7.2. Study time points and evaluation items**

**7.2.1. Screening**

(1) Participant characteristics

Age, sex, height, weight, medical history, comorbidities, medications (antihypertensive drugs, sleep-inducing drugs, antipsychotics, and central nervous system agents), ASA physical status, clinical frailty scale, surgery procedure, laboratory values of the latest surgery (hemoglobin, creatinine, and serum albumin).

(2) Vital signs

Noninvasive blood pressure (NIBP) and pulse rate will be measured in the ward after obtaining informed consent for this research.

**7.2.2. Pre-induction of general anesthesia**

(1) Vital signs

Before starting preoxygenation, NIBP and heart rate were measured twice as baseline vital signs.

**7.2.3. From the administration of sedatives to loss of consciousness**

(1) Vital signs

Blood pressure and heart rate will be measured at 1-min intervals.

(2) Time from the beginning of sedative drug administration to loss of consciousness.

(3) Injection pain

Participants will be asked a question about pain on injection after the start of sedative drug administration.

**7.2.4. From loss of consciousness to tracheal intubation**

(1) Vital signs

Blood pressure and heart rate will be measured at 1-min intervals.

**7.2.5. From the success of intubation to 3 minutes after intubation**

(1) Vital signs

Blood pressure and heart rate will be measured at 1-min intervals.

(2) Drug dose for induction of anesthesia

The number or dose of using any type of vasopressor between the start of sedative administration and 3 min after tracheal intubation

The dose of the trial drug for induction

**7.2.6. The day after surgery**

Occurrence of AEs

**7.2.7. Discontinuance**

1) Before starting anesthesia induction

In the cases where 1), 2), 6), or 7) of “6.5.5.1. Discontinuation criteria” will be applied.

Since the test drug will not be administered, no items to be observed will occur.

2) From induction of anesthesia to the analysis period

AEs will be monitored during anesthesia, which is routine practice, and by general postoperative examination, which is routine clinical practice.

**7.3. Evaluation method**

Not applicable.

**8. Outcomes**

**8.1. Primary outcome**

The primary outcome will be the incidence of hypotension between the start of propofol or remimazolam and 3 min after tracheal intubation. The definition of hypotension is an MBP <65 mmHg measured by NIBP.

**8.2. Secondary outcome**

- - 1. Maximum MBP 3 min after tracheal intubation
    2. Minimum heart rate after loss of consciousness.
    3. The number or dose of any type of vasopressor between the start of sedative administration and 3 min after tracheal intubation
    4. The time from the start of sedative drug administration to loss of consciousness. The loss of consciousness is defined as the loss of both the response to verbal stimuli and the reflex of the eyelashes. Loss of response to verbal stimuli was confirmed by calling his/her name every 10 s from the start of sedative drug administration.
    5. The dose of drugs used for anesthesia induction (*i.e.*, propofol or remimazolam)
    6. Incidence of injection pain. Participants will be asked a question about pain on injection after the start of sedative drug administration.

Pain on injection will be estimated by the following four-point scale:

0 = no pain

1 = mild pain (pain reported only in response to questioning and without any behavioral signs)

2 = moderate pain (pain reported in response to questioning and accompanied by a behavioral sign, or pain reported spontaneously without questioning)

3 = severe pain (strong vocal response or response accompanied by facial grimacing, drawing back the arm, or tears).

- - 1. Characteristics of the participants (age, sex, height, weight, medical history, comorbidity, medications [antihypertensive drugs, sleep-inducing drugs, antipsychotics, and central nervous system agents], ASA physical status, clinical frailty scale, surgery procedure, laboratory values of the latest surgery [hemoglobin, creatinine, and serum albumin]).
    2. Exploring factors associated with the incidence of hypotension

**8.3. Safety outcome**

AEs.

**9. Statistical analysis**

**9.1. Definition of an analysis set**

**9.1.1 Full analysis set (FAS)**

The full analysis set included all enrolled participants, administered the test or control drug, and obtained outcome data.

**9.1.2. Per protocol set (PPS)**

PPS is defined as participants excluded from FAS that have the following serious violations of the rules of the research protocol: selection criteria, exclusion criteria, concomitantly banned drugs, or concomitant therapy.

**9.1.3. Safety analysis set (SAS)**

The safety analysis set included all participants who will be enrolled, administered the test or control drug.

**9.2. Calculation of sample size**

The frequency of hypotension associated with the induction of general anesthesia was estimated to be 40% based on cases similar to our protocol extracted from our institutional data for a randomly selected month. In a previous study, the relative risk of remimazolam to propofol for the frequency of hypotension associated with induction of anesthesia was reported to be 0.28. If Fisher’s exact probability test with a type I error set at 5% and a power greater than 80% will be performed, it was estimated that at least 84 participants per group would be needed. Considering a dropout, we decided to include 45 participants in each group (*i.e.*, 90 in total).

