**6.2. Sample size**

Ninety cases (standard treatment group: 45 cases and trial drug group: 45 cases)

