**9.3. Statistical methods**

**9.3.1. Analysis for primary outcome**

**9.3.1.1. Main analysis**

The incidence of hypotension in the intervention and control groups will be calculated. The odds ratio (OR) with 95% confidence intervals (CIs) between both groups was calculated. The incidence of hypotension between the two groups will be compared using the Mantel−Haenszel χ^2^ test and adjusted OR for the stratification factor for randomization. Homogeneity across strata will be assessed using the Breslow-Day test.

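### Section 9.2 gives 84 participants per group as the minimum but enrols 45 per group; its own inputs show that 84 is the total (42 per group)

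*Protocol*

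**What the plan says.** Protocol Section 9.2 sizes the trial on Fisher's exact test with a "type I error set at 5% and a power greater than 80" percent. The propofol rate is put at 40%, from one month of institutional data. For the effect, "the relative risk of remimazolam to propofol for the frequency of hypotension associated with induction of anesthesia was reported to be 0.28". The result follows: "at least 84 participants per group would be needed. Considering a dropout, we decided to include 45 participants in each group", which the section itself totals to 90. It states neither a dropout rate nor whether the test is one- or two-sided.

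Section 6.2 gives the same planned size: "Ninety cases (standard treatment group: 45 cases and trial drug group: 45 cases").

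Section 9.3.1.1 makes the primary comparison a Mantel-Haenszel chi-square test, with an "adjusted OR for the stratification factor for randomization". Fisher's test appears as a planned analysis only for injection pain, in Section 9.3.2.

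**The concern.** The two halves of the sizing statement contradict each other. Allowing for dropout moves a sample size up, yet here it appears to move from 84 to 45 per group. Nothing elsewhere in the protocol explains the step, and the enrolled number is consistent wherever it appears, so the suspect figure is the minimum.

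This is the only justification of size in the protocol. An ethics committee, journal or meta-analyst who reads it as printed sees a trial with 45/84 = 54% of its own stated minimum. That matters most for a null result, because Section 2.5 says that a negative finding would indicate little need to change current practice.

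**Working it through.** **Inputs (Section 9.2).** Propofol rate p1 = 0.40. Relative risk 0.28, so p2 = 0.28 × 0.40 = 0.112 and the difference d = 0.288. Type I error 0.05, assumed two-sided (z = 1.960). Power 80% (z = 0.842). Allocation 1:1 (Section 6.2).

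**Step 1: the usual formula without continuity correction.** The mean rate is (0.40 + 0.112)/2 = 0.256.

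n = [1.960 × √(2 × 0.256 × 0.744) + 0.842 × √(0.40 × 0.60 + 0.112 × 0.888)]² / d²

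= [1.960 × 0.6172 + 0.842 × 0.5826]² / 0.0829 = 34.8, so 35 per group.

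**Step 2: with continuity correction, the common approximation to Fisher's test.**

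n' = (n/4) × [1 + √(1 + 4/(n × d))]² = (34.8/4) × [1 + √1.399]² = 41.5, so 42 per group.

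The total is 2 × 42 = **84**. This reproduces the protocol's number exactly, as a total.

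**Step 3: exact two-sided Fisher power by full enumeration, 0.40 against 0.112.**

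| Per group | Power |
|---|---|
| 39 | 79.4% |
| 40 | 80.8% |
| 42 | 83.3% |
| 45 | 85.0% |
| 84 | 99.0% |

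Exact enumeration first passes 80% at 40 per group. The figure 42 therefore matches the continuity-corrected approximation rather than the exact calculation. Either way, 45 per group is enough and 84 per group is far more than a target just above 80% needs.

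**Step 4: could 84 per group come from another reading of the inputs?** Each pair is uncorrected, then continuity-corrected.

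- One-sided 5%, 80% power: 28 or 34 per group.
- Two-sided, 90% power: 47 or 53.
- 0.28 read as an odds ratio, 80% power: 53 or 61.
- To need about 84 per group at 80% power, the relative risk would have to be about 0.48 (corrected) or 0.50 (uncorrected), not 0.28.

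None of the variants tried gives 84 per group at 80% power with the stated effect.

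**Step 5: the dropout margin.** 90 − 84 = 6, and 6/90 = 6.7%. The protocol does not state this rate; it follows from reading 84 as the total.

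**Step 6: the planned primary test.** The Mantel-Haenszel chi-square test was simulated (100,000 runs) with two strata of about equal size. The propofol rate was either 40% in both strata or 30% and 50%, with a relative risk of 0.28 throughout.

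| Per group | Continuity-corrected | Uncorrected |
|---|---|---|
| 42 | 81.5% to 82.6% | 88.4% to 89.2% |
| 45 | 85.0% to 86.0% | 90.1% to 91.1% |

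Fisher's test at 45 per group has 85.0%, so the planned test has at least as much power at the enrolled size.

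**The case against.** The strongest reply is that this is a slip of wording with no consequence. The planned size is stated consistently as 45 + 45 = 90, it delivers more than 80% power on the stated inputs, and correcting the sentence changes no enrolment, design or analysis. That stands as far as the design goes. It does not rescue the sentence, which gives a false minimum in the one place where the trial's size is justified.

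A reader might infer from the printed text that the trial is underpowered at 54% of its requirement. The documents do not support that: the 84 matches the total from the protocol's own inputs, and 84 per group would give 99.0% power against a target just above 80%.

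A reader might also infer that sizing on Fisher's test leaves the primary Mantel-Haenszel test without adequate power. That does not follow either. Sizing on an unstratified Fisher test is common, and step 6 shows no loss at 45 per group. Details of power for the primary test may also sit in a statistical analysis plan that is not shown.

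Three cautions remain. Reading 84 as the total is a strong inference, not something the protocol says. Two-sidedness is assumed. The margin of 6 is inferred, and under Section 5.2 patients with low pre-induction pressure or a failed first intubation are treated as excluded cases rather than dropouts, so the protocol does not establish that 6 covers every loss. Exact Fisher power nevertheless stays above 80% down to 40 per group.

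**Conclusion.** The point holds as an error in the stated requirement. The figure of 84 per group contradicts the 45 per group in the next sentence and in Section 6.2, and it is too large by a factor of two. The value that fits the inputs is 42 per group, 84 in total, and the planned 90 meets the stated power (85.0% by exact Fisher at 45 per group, 83.3% at 42).

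This rests on the 40% rate and the relative risk of 0.28 as given, a two-sided 5% test and equal allocation. It is a check of the arithmetic; it does not test whether those two assumptions are realistic. The difference between the sizing test and the primary test is a side note only.

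**What to change.** First check the original calculation. If it confirms the reading above, revise Section 9.2 to say that at least 84 participants in total (42 per group) are needed, that the test is two-sided, and that enrolling 90 leaves room for 6 losses (6.7%). If the original calculation really gave 84 per group, the stated inputs are not the ones used, and both they and the planned 90 need to be revisited.

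Optionally, add the power of the planned Mantel-Haenszel test. If so, give it together with the choice on continuity correction, which Section 9.3.1.1 leaves open: about 85% corrected to 90% uncorrected at 45 per group, and about 81–83% to 88–89% at 42. A single figure without that choice would not be safe.

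If the reading is confirmed, the cost is one corrected sentence, with no extra patients and no change to the design or analysis.

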**9.3. Statistical methods**

**9.3.1. Analysis for primary outcome**

**9.3.1.1. Main analysis**

The incidence of hypotension in the intervention and control groups will be calculated. The odds ratio (OR) with 95% confidence intervals (CIs) between both groups was calculated. The incidence of hypotension between the two groups will be compared using the Mantel−Haenszel χ^2^ test and adjusted OR for the stratification factor for randomization. Homogeneity across strata will be assessed using the Breslow-Day test.

**9.3.1.2. Additional analysis for primary outcome**

**1) Subgroups for analysis:** The subgroup for analysis will be generated as the following factors:

- 1. Charlson comorbidity index ≤2 or ≥3
  2. Clinical frailty scale ≤4 or ≥5
  3. Hypertension in the ward the day before surgery is defined as SBP ≥140 mmHg or diastolic blood pressure ≥90 mmHg
  4. Age (<90 or ≥90 years old)

The proportion of people aged ≥90 years in the total Japanese population is 2.1% (approximately 2.61 million), which is significantly different from the 12.8% (approximately 16.19 million) of people in their 80s. This was determined based on the assumption that this group is particularly affected by adverse drug reactions and circulatory instability.

**2) Sensitivity analysis of the primary analysis:** The OR with 95% CI adjusted for preinduction blood pressure (SBP ≥160 mmHg or <160 mmHg) will be calculated using the Mantel−Haenszel χ^2^ test. This cut-off point for SBP was as follows: (1) calculated based on the median value in the historical data of our institution for similar age groups; (2) and was determined regarding the exclusion criteria for blood pressure in a previous study on the efficacy and safety of remimazolam.

**3) The absolute risk reduction values with 95% CI** adjusted for stratification will be calculated using Mantel−Haenszel risk differences.

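### In the planned treatment comparisons, pre-induction pressure enters only as systolic pressure cut at 160 mmHg; a model with the stratum plus continuous mean pressure would be a cheap improvement

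*Protocol*

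**What the plan says.** - **Outcome.** Protocol Section 8.1 defines hypotension as a cuff MBP below 65 mmHg during the induction window.
- **Baseline.** Section 7.2.2 states that "NIBP and heart rate were measured twice as baseline vital signs", before preoxygenation. Section 5.2 (criterion 14) also uses pre-induction mean pressure, excluding patients below 70 mmHg.
- **Primary analysis.** Section 9.3.1.1 uses a Mantel-Haenszel test and an "adjusted OR for the stratification factor for randomization". Under Section 6.4.4 that factor is ward hypertension, yes or no.
- **Sensitivity analysis.** Section 9.3.1.2, item 2: "The OR with 95% CI adjusted for preinduction blood pressure (SBP ≥160 mmHg or <160 mmHg) will be calculated", again by Mantel-Haenszel. The cut is fixed in advance and supported by a historical institutional median and by a previous study's exclusion criteria. Item 2 does not name the stratum. Item 3, the risk difference, does say that it is adjusted for stratification.
- **Exploratory model.** Section 9.3.2 lists a logistic regression for factors associated with hypotension. Pre-induction hypertension, ward hypertension and induction drug are three of its 12 predictors.

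**The concern.** The protocol itself treats prior pressure as prognostic. Section 6.4.4 stratifies because patients with lower usual pressure may cross 65 mmHg more readily. The closest measure of this, MBP minutes before induction, is collected in everyone but is not used as such in any planned estimate of the treatment effect on the primary outcome.

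The one analysis that does use pre-induction pressure has two weaknesses. It takes systolic rather than mean pressure and reduces it to two levels, so a chance imbalance in baseline MBP between arms of 45 is only partly corrected. As worded, it also appears to put systolic pressure in place of the stratum. If its odds ratio differed from the primary one, a reader could not tell whether the added covariate or the missing stratum was the reason. At stake are some precision and the usefulness of the sensitivity analysis. The validity of the primary test is not in question.

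**Working it through.** **1. The plan's own figure.** Section 9.2 gives a control risk p1 = 0.40 and a relative risk of 0.28, so p2 = 0.40 × 0.28 = 0.112. The difference is d = 0.288 and the mean risk is 0.256. With two-sided 5% (sidedness is not stated) and 80% power:

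n = [1.96·√(2 × 0.256 × 0.744) + 0.8416·√(0.40 × 0.60 + 0.112 × 0.888)]² / 0.288² = (1.210 + 0.490)² / 0.0829 ≈ 34.8, so 35 per group.

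With continuity correction: (34.8/4)·[1 + √(1 + 4/(34.8 × 0.288))]² ≈ 41.5, so 42 per group, or 84 in total. Section 9.2 instead says "at least 84 participants per group would be needed" and then "we decided to include 45 participants in each group". The 84 reproduces as a total and not per group. That is a separate matter; here it only shows that 42 to 45 per group is the size to examine. Exact two-sided Fisher power is 83.3% at 42 per group and 85.0% at 45.

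**2. Can the exploratory model do this job?** Expected events at 45 per group are 45 × 0.40 + 45 × 0.112 = 18 + 5.04 ≈ 23. With 12 predictors that is 23/12 ≈ 1.9 events per predictor, too few for a dependable adjusted treatment estimate. A model with treatment, stratum and MBP has 23/3 ≈ 7.7.

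**3. What the systolic split retains.** For a normal variable, a median split keeps 2/π ≈ 64% of the variance. If systolic pressure and MBP correlate at c (assumed), the split explains c² × 0.637 of MBP variance: 31% at c = 0.7, 41% at 0.8 and 52% at 0.9. About half to two-thirds of the baseline MBP variation is left unadjusted.

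**4. Effect on power (simulation).** There were 3,000 trials per scenario, with blocks of 4 within ward-hypertension strata. Assumptions that are not in the protocol: normal variables; ward pressure correlated 0.5 with pre-induction MBP and split at its median; systolic pressure correlated 0.85 with MBP and split at its median; r is the correlation of baseline with lowest MBP. MH-ward is the planned primary test, MH-SBP is item 2 as worded, and Logistic is the likelihood-ratio test for treatment with stratum plus continuous MBP. Figures are % rejections at 45 per group:

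| r | 40 vs 11.2: MH-ward | MH-SBP | Logistic | 40 vs 20: MH-ward | MH-SBP | Logistic | Null: MH-ward | Null: Logistic |
|---|---|---|---|---|---|---|---|---|
| 0 | 90.8 | 90.4 | 91.5 | 55.1 | 54.7 | 56.0 | 4.5 | 5.3 |
| 0.2 | 90.6 | 90.4 | 91.4 | 55.6 | 55.7 | 57.7 | 4.9 | 5.6 |
| 0.3 | 90.4 | 90.9 | 92.2 | 54.1 | 54.5 | 57.8 | 4.5 | 5.4 |
| 0.4 | 90.0 | 90.4 | 92.1 | 55.5 | 56.3 | 60.6 | 4.7 | 6.1 |
| 0.5 | 91.1 | 91.7 | 94.1 | 58.4 | 59.0 | 64.9 | 5.5 | 5.7 |
| 0.6 | 91.1 | 92.4 | 95.4 | 55.8 | 57.5 | 65.6 | 5.1 | 4.8 |

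The Monte Carlo standard error is √(0.9 × 0.1/3000) ≈ 0.5 point near 90% and about 0.9 near 55%. At 42 per group the gains of Logistic over MH-ward are similar: for 40 vs 11.2, 0.4 point at r = 0 (88.8 to 89.2), 1.7 at r = 0.3 (88.0 to 89.7) and 5.7 at r = 0.6 (89.3 to 95.0); for 40 vs 20, 11.3 points at r = 0.6 (51.5 to 62.8).

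**5. The missing stratum.** Adding the ward stratum to the systolic split changed power by 1 point or less throughout. Its omission therefore matters for interpretation and hardly at all for power.

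**The case against.** The strongest reply is that nothing here is wrong. The primary analysis respects the stratified design, needs no linearity assumption and exceeds 80% power at the design effect. The 160 mmHg cut was fixed in advance with reasons. A sensitivity analysis may legitimately vary the adjustment set, and the form of a covariate is often left to the statistical analysis plan. All of this stands, except that the protocol does fix the covariate's form here, so the choice is open to comment.

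A reader might infer more than the protocol supports:

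- *That pre-induction pressure is used nowhere else.* It is also an exclusion criterion and a predictor in the exploratory model of Section 9.3.2, whose coding is not stated. The point holds only for the planned analyses of the treatment effect on the primary outcome.
- *That the plan abandons its stratification factor.* The primary test, its odds ratio and the Mantel-Haenszel risk difference all adjust for it. One sensitivity analysis does not name it.
- *That the trial wastes power.* A sensitivity analysis carries no confirmatory power, so changing it alone gains none. The power figures apply only if the fuller model becomes primary. They rest on a correlation absent from the protocol and nearly vanish at the design effect when r is 0.2 or less.

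Part of the gain is also test size: the logistic test rejected in 4.8% to 6.1% of null trials.

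**Conclusion.** The point holds as an inexpensive improvement to the sensitivity analysis. The outcome's own baseline is collected in every patient, but for the treatment effect it is used only as a two-level systolic variable, without the stratum named.

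If the fuller model were used for the main comparison, the gain at the design effect would be about 0 to 1 point for r = 0 to 0.2 and about 2 to 6 points for r = 0.3 to 0.6. With true rates of 40% vs 20% it would be about 3 to 11 points for r = 0.3 to 0.6, allowing for simulation error. Up to about 1 point of each gain is test-size inflation. The smaller effect is an assumption, but not a remote one: the planning relative risk of 0.28 comes from a single cited study, and Section 2.3 quotes 33% vs 60% for treated hypotension during anaesthesia, a ratio of 0.55, though for a different endpoint and period. The main benefit that needs no assumed correlation is interpretive: a sensitivity analysis that adds one covariate to the primary adjustment can be read directly against it.

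**What to change.** Before unblinding, replace or supplement item 2 of Section 9.3.1.2 with a prespecified logistic model containing treatment, the ward-hypertension stratum and continuous pre-induction MBP, defined as the mean of the two readings in Section 7.2.2. Report the standardised risk difference with its 95% CI, which sits on the same scale as the Mantel-Haenszel risk difference already planned in item 3. If the 160 mmHg analysis is kept, state whether the stratum stays in it. Making the new model primary is optional; if that is done, keep the Mantel-Haenszel result as supportive.

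The cost is analysis wording and the revision procedure of Section 13.3, with no new data, visits or patients. The downsides are a linearity assumption for MBP on the logit scale and a conditional odds ratio that is not comparable with the Mantel-Haenszel one, which is why the risk difference should be reported.
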